
### Measurements

To measure the study objectives, the following outcomes will be captured: (1) *pain intensity*, (2) *pain impairment*, (3) *quality of life*, (4) *physical and emotional functionality*, (5) *pain acceptance*, and (6) *anxiety and depressive symptoms*. A list of measurement instruments is presented in Table 2.

**Table 2. T2:** Measurement instruments^a^.

Questionnaire	Pre	Post	Follow-up
Basic data			
Demographics (age, sex, education, etc)	✓	—^b^	—
Primary outcomes			
Pain intensity and pain impairment (WHYMPI^c^)	✓	✓	✓
Quality of life (AQoL-8D^d^)	✓	✓	✓
Secondary outcomes			
Physical functionality (WHYMPI subscales)	✓	✓	✓
Emotional functionality (WHYMPI subscales)	✓	✓	✓
Pain acceptance (CPAQ-D^e^)	✓	✓	✓
Anxiety (GAD-7^f^)	✓	✓	✓
Depression (PHQ-9^g^)	✓	✓	✓

a Treatment as usual (TAU) includes additional assessments due to the waiting period.

b Not applicable.

c WHYMPI: West Haven-Yale Multidimensional Pain Inventory [23].

d AQoL-8D: Assessment of Quality of Life—8 Dimension [24].

e CPAQ-D: Chronic Pain Acceptance Questionnaire, German version [25].

f GAD-7: Generalized Anxiety Disorder-7 [26].

g PHQ-9: Patient Health Questionnaire-9, German version [27].

#### Primary Outcomes

Primary outcomes include pain intensity, pain-related impairment, and health-related quality of life. To assess pain intensity and impairment, the German version of the WHYMPI will be used [23]. The WHYMPI is a comprehensive 52-item questionnaire comprising 12 subscales that assess the multidimensional impact of chronic pain on patients’ daily lives. It includes scales for pain severity, pain-related interference, perceived life control, and affective distress. The inventory also evaluates patients’ perceptions of significant others’ responses to their pain (eg, solicitous or negative behaviors) and the frequency of engagement in everyday activities, including a general activity level score. Responses are recorded on a 7-point Likert scale.

Health-related quality of life will be measured using the German version of the Assessment of Quality of Life—8 Dimension (AQoL-8D) instrument [24]. The AQoL-8D is a validated multiattribute utility measure consisting of 35 items that cover 8 key dimensions of quality of life: independent living, happiness, mental health, coping, relationships, self-worth, pain, and senses. Response options vary between 4-point and 6-point scales depending on the domain. The AQoL-8D yields a psychometric score that reflects overall health-related quality of life.

#### Secondary Outcomes

Secondary outcomes include physical and emotional functioning, patients’ global improvement, pain acceptance, anxiety, and depressive symptoms. To assess pain acceptance, the German version of the Chronic Pain Acceptance Questionnaire (CPAQ-D) will be used [25]. The CPAQ-D contains 20 items across 2 subscales: “Activity engagement” and “Pain willingness.” Responses are given on a 7-point scale, with higher scores indicating greater acceptance of chronic pain. Depressive symptoms will be assessed using the Patient Health Questionnaire-9 (PHQ-9) [27] and the Generalized Anxiety Disorder 7 (GAD-7) for anxiety symptoms [26]. The PHQ-9 includes 9 items that correspond to the *DSM-IV* (*Diagnostic and Statistical Manual of Mental Disorders, Fourth Edition*) criteria for depression and are rated on a 4-point scale (0=not at all to 3=nearly every day). Severity is categorized based on the total score (0‐4=minimal, 5‐9=mild, 10‐14=moderate, 15‐19=moderately severe, and ≥20=severe depression). The GAD-7 comprises 7 items rated on a 4-point scale and assesses the frequency of anxiety symptoms over the past 2 weeks. Severity categories include minimal, mild, moderate, and severe anxiety. Patients’ subjective global improvement and perceived functionality are additionally derived from specific subscales of the WHYMPI, including general activity level and affective distress, as indicators of change in physical and emotional functioning over the course of the intervention.

### Statistical Analysis

All statistical analyses will be conducted using the statistical software R (version 4.5.0; R Core Team). For the PP analysis, “full adherence” will be defined a priori. Participants must complete at least 9 out of the 12 intervention modules (≥75% completion rate) within the intended 12-week intervention period to be included in the PP dataset. Thresholds such as completing ≥75% of modules are commonly reported in digital intervention research to operationalize adherence criteria, although empirical justification varies across studies, and this threshold is considered consistent with existing eHealth adherence frameworks [28]. Participants who complete fewer than 9 modules or who finish all modules in an implausibly condensed time frame that violates the intended weekly structure will be excluded from the PP dataset. First, all primary and secondary outcomes as well as participant demographics and baseline characteristics will be analyzed descriptively (means, SDs, and frequencies), both for the total sample and stratified by the study group (EGpsych, EGcomp, and TAU). To examine intervention effects, mixed models for repeated measures will be used as the primary analytic approach. The mixed models for repeated measures allow the inclusion of all available outcome data and accommodate unequal assessment schedules between groups due to the 6-month waiting period in the TAU condition. The primary randomized comparison will focus on the matched assessment approximately 6 months after baseline, corresponding to the 3-month follow-up in the experimental groups (T2) and the end of the waiting period in the TAU group (TAU-T1). For each primary and secondary outcome, models will include fixed effects for group (EGpsych vs EGcomp vs TAU), time (baseline vs matched 6-mo assessment), and the group × time interaction. A participant-specific random intercept will be included to account for within-person correlation. The group × time interaction will be used to test differential change between conditions. Holm-corrected post hoc contrasts will be applied for pairwise comparisons where applicable. If model assumptions are violated, appropriate robust methods will be considered. Outcome data collected in the TAU group after participants have received access to CHRONIC (eg, TAU-T2 and TAU-T3) will not be included in the primary randomized comparison because TAU no longer represents a control condition at that stage. Post-waitlist TAU data will instead be analyzed separately and within-group (exploratory) to describe changes following delayed program access. Exploratory analyses within each study arm will be reported descriptively. However, comparisons across nonmatched time intervals will not be interpreted as randomized sensitivity analyses. When a significant main or interaction effect is detected, Holm-corrected post hoc tests will be applied to determine the specific time points and group differences, while controlling for the family-wise error rate.

All analyses will be conducted according to both the intention-to-treat and PP principles. The intention-to-treat approach includes all randomized participants in the groups to which they were assigned, regardless of adherence to the intervention, thereby maintaining the benefits of randomization and reflecting real-world applicability. In contrast, PP analyses include only those participants who fully adhered to the intervention protocol, offering insights into the intervention’s efficacy under ideal conditions. Participants must complete at least 9 out of 12 modules (≥75%) within the intended 12-week intervention period to be included in the dataset. Participants below this threshold will be excluded from PP analyses. Comparing both approaches helps assess the robustness and generalizability of findings. Subgroup analyses may be conducted to explore whether intervention effects differ across specific participant characteristics, such as baseline pain severity, age, or gender. These analyses can help identify moderators of treatment effects and thereby contribute to a more personalized understanding of intervention efficacy. Moderator analyses will be exploratory in nature and interpreted with caution due to limited power. Adherence outcomes, including the number of completed modules, log-in frequency, and intervention dropout, will be compared descriptively and inferentially between EGpsych and EGcomp to evaluate potential differences in engagement patterns. Missing data will be handled using multiple imputation, which estimates missing values based on the observed data and includes random variation across imputations. This approach reduces bias and increases statistical power compared to complete case analyses, as it uses all available data while accounting for uncertainty introduced by the missingness [29].

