## Introduction

### Background

Approximately 12 million individuals in Germany are affected by chronic pain [1], representing around 14% of the national population. Alongside physiotherapy and medication, psychotherapeutic interventions have proven effective in treating chronic pain [2]. However, extensive waiting times of several months before patients receive access to specialized multidisciplinary pain services represent a major barrier to adequate pain management and contribute to delayed treatment initiation and symptom chronification [3], highlighting the urgent need for scalable, cost-effective treatment options. To address this gap, the German government implemented the Digital Healthcare Act (Digitale-Versorgung-Gesetz) on December 9, 2019, enabling physicians and psychotherapists to prescribe reimbursable digital health applications. Parallel to these developments, international research has demonstrated that digital psychological interventions for chronic pain, and particularly those based on acceptance and commitment therapy (ACT) and cognitive behavioral therapy (CBT), can effectively reduce pain interference and distress compared with waitlist control conditions [4-6]. For example, the German online ACT program ACTonPain showed medium effects on pain-related functioning and pain acceptance in individuals with long-standing pain symptoms, with improvements sustained at follow-up. Importantly, ACTonPain compared guided and unguided ACT delivery and found significant improvements in both intervention arms relative to waitlist control, while guided ACT demonstrated stronger effects and lower attrition rates, highlighting the potential clinical value of blended or therapist-supported components in digital pain treatment [4]. However, most existing digital interventions primarily reflect unimodal treatment formats focusing on psychological or physical mechanisms in isolation. Given the multidimensional nature of chronic pain and the limitations of unimodal approaches, there is a need for integrated, multimodal digital interventions that combine psychotherapeutic, behavioral, and physical activation strategies within a single framework. The rationale for developing a multimodal digital intervention is further supported by research demonstrating that chronic pain outcomes improve most when biological, psychological, and behavioral mechanisms are targeted simultaneously. Meta-analytic findings show that multimodal pain rehabilitation programs outperform unimodal approaches in terms of pain interference, disability, and emotional functioning [7,8]. Digital delivery formats are increasingly used to operationalize such biopsychosocial principles: blended or hybrid pain interventions combining psychological content, physical exercise components, and self-management strategies have reported clinically meaningful improvements in pain intensity, mobility, and quality of life [9,10]. These results suggest that integrating physiotherapeutic and psychological principles within a single digital platform may strengthen treatment effects by addressing multiple pain mechanisms concurrently rather than sequentially. The web-based application CHRONIC is designed to address this care gap for individuals with chronic pain. CHRONIC is grounded in ACT [11] as a third-wave cognitive-behavioral approach and integrates selected traditional CBT techniques (eg, cognitive restructuring and behavioral activation), mindfulness-based strategies [12], and physiotherapeutic exercises into a coherent, multimodal program. The goal is to offer a comprehensive educational and therapeutic program that equips users to manage their pain condition effectively. Given the multidimensional nature of chronic pain, a multimodal treatment approach—integrating biological, psychological, and social elements—is considered necessary [13]. Skelly et al [14] found that unimodal nonpharmacological interventions for chronic pain—such as isolated exercise or psychological therapies—often produce only modest and short-term effects. Long-term benefits were rare, and methodological heterogeneity limited the strength of evidence. The authors conclude that single-modality treatments fail to address the biopsychosocial complexity of chronic pain, highlighting the need for integrated, multimodal approaches.

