### Study Design

This is an interventional, randomized controlled trial (RCT) with 3 parallel arms, including a nonblinded TAU group. The 2 experimental groups (EGpsych and EGcomp) complete 3 assessments: baseline prior to intervention start (T0), postintervention at week 12 (T1), and a 3-month postintervention follow-up, which represents the primary end point (6 mo after baseline, T2). In contrast, the TAU group follows an extended assessment schedule due to the 6-month waiting period: TAU participants complete a baseline measurement at study entry (T0), a second assessment following the 6-month waiting period and immediately before accessing the intervention (TAU-T1), a postintervention assessment after completing the 12-week program (TAU-T2), and a 3-month follow-up (TAU-T3). The 2 experimental groups receive access to the digital self-help program CHRONIC. Participants in the TAU group will receive access to the CHRONIC program with standardized computer-generated feedback (EGcomp version) after completing the 6-month waiting period. The 6-month waiting period for the TAU group was selected for 3 reasons. First, it reflects real-world access barriers in specialized pain services in Germany, where waiting times of 4 to 6 months are frequently reported for multidisciplinary pain treatment programs and specialist behavioral interventions, making this duration clinically realistic rather than arbitrary [3,23]. Second, extending the waiting period increases the likelihood of detecting natural symptom progression and pain chronification effects, allowing a meaningful comparison with the intervention arms and preventing artificially low variance caused by very short control periods. Third, choosing a 6-month window enables methodological alignment with the intervention design: since participants in the experimental arms undergo a 12-week treatment followed by a 3-month follow-up, the 6-month TAU period ensures comparable temporal exposure before receiving access to the program. The groups differ in the type of feedback received after each module: participants in the EGpsych receive individualized feedback written by the study team, whereas participants in the EGcomp receive standardized, template-based, computer-generated feedback. The study design is illustrated in Figure 1.

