Modules are time-locked to ensure standardized intervention exposure because the intervention is designed to run over a fixed 12-week period. Each new module becomes available exactly 7 days after the previous module has been released. Participants cannot access future modules ahead of schedule, and early progression or skipping forward is technically prevented. The program cannot be paused. All participants have a fixed consecutive 12-week access period, after which access to the intervention ends automatically. If participants choose not to complete a module in the week it becomes available, the next module is still released on schedule 7 days later. This allows participants to complete multiple outstanding modules in a shorter interval later on, reducing the time gaps between sessions while still operating within the fixed 12-week intervention window. All completion times and access patterns are recorded through backend timestamps and will be evaluated in adherence. To support structured engagement and continuity in self-monitoring, brief intersession assessments are implemented within the platform workflow. Before participants can begin the next module, they are required to complete a short check-in assessment referring to the preceding week, based on subscales derived from the West Haven-Yale Multidimensional Pain Inventory (WHYMPI; part 1 “Pain experience statements” and part 3 “Patient activity”). These assessments are integrated directly into the platform interface and are automatically presented at the start of each new session. The check-ins occur once per week, require approximately 2 minutes to complete, and refer to the participant’s experiences during the previous 7 days. Modules cannot be accessed until the corresponding check-in is completed, ensuring a consistent measurement structure across participants. There is no fixed time of day for completion since the brief assessment appears immediately when the new module is opened and remains available until submitted. These data are visualized in real time on the user’s personal dashboard as a line graph based on the summed scores to support self-monitoring. After each module, participants in the experimental groups receive motivational feedback—either individualized or computer-generated, depending on group assignment—delivered via the app and email shortly after session completion. Feedback is only triggered following the completion of a module. The feedback procedure differs between the 2 intervention conditions. In the EGpsych arm, feedback is written individually by psychologists from the study team. All potential feedback providers hold a university degree in psychology and have additional clinical experience in working with individuals with chronic pain. Feedback integrates participant-specific information derived from the weekly self-assessments. Messages are delivered asynchronously in written text format via the platform interface. In contrast, participants in the EGcomp arm receive standardized feedback messages prewritten by psychologists from the study team based on a fixed template system. These messages include the same structural components as in EGpsych (completion acknowledgment, motivational reinforcement, psychoeducational element, and goal reminder), but they do not integrate individual self-assessment data or module-specific personal content. The feedback is identical across all EGcomp participants and does not vary based on adherence patterns or timing. This standardized structure ensures consistency in length, tone, and delivery frequency across participants while maintaining methodological separation from tailored guidance. In both intervention arms, feedback messages are delivered asynchronously via the platform and email notification within 24 hours following module completion, and participants cannot respond to feedback in either condition. The feedback texts contain approximately 100 to 150 words per module. If participants complete multiple modules within a single day (catch-up use), EGpsych feedback is not provided separately for each module. Instead, one feedback message is provided referencing the last completed module and comparing the most recent assessment with the prior assessment, thereby reflecting the latest available change pattern rather than generating multiple module-specific feedback messages. Such accelerated completion patterns and potential overlaps in assessment windows are captured via timestamps and will be considered in adherence metrics and per-protocol (PP) definitions.

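### The two-level time factor leaves the week-12 scores of both CHRONIC arms out of the model, contrary to its stated rationale, and the plan does not say whether the imputation uses them

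*Protocol article*

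**What the plan says.** Four statements in the protocol article bear on this.

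- **Rationale (Statistical Analysis).** "The mixed models for repeated measures allow the inclusion of all available outcome data and accommodate unequal assessment schedules between groups".
- **Model (Statistical Analysis).** For each primary and secondary outcome the fixed effects are group, "time (baseline vs matched 6-mo assessment), and the group × time interaction". The dependence structure is one term: "A participant-specific random intercept will be included to account for within-person correlation".
- **Schedule (Study Design and Table 2).** The two experimental arms have "baseline prior to intervention start (T0), postintervention at week 12 (T1), and a 3-month postintervention follow-up", and Table 2 lists every outcome instrument at all three visits. TAU has no assessment between baseline and the end of its 6-month wait.
- **Missing data (Statistical Analysis).** "Missing data will be handled using multiple imputation, which estimates missing values based on the observed data". The section adds that imputation draws on everything available. It names no imputation variables.

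The only outcome data that the section expressly keeps out of the randomized comparison are TAU scores taken after program access. It gives no reason for leaving out T1 in EGpsych and EGcomp.

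**The concern.** A mixed model with all post-baseline visits protects against loss that depends on earlier observed scores, because those scores inform the expected value of the missing one. With only baseline and 6 months in the model, that protection rests on baseline alone. T1 lies closer in time to the 6-month visit and is measured after treatment, so it is likely to carry more information both about the missing score and about who is lost.

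Two features of the document make this more than formal. The Sample Size section recruits 200 for a requirement of 114, which allows for loss of 1 − 114/200 = 43%. The Background cites an online trial in which "guided ACT demonstrated stronger effects and lower attrition rates", so loss may also differ between EGpsych and EGcomp, a comparison that the Study Objectives list. If participants doing worse at week 12 are lost more often, the CHRONIC arms look better at 6 months than they are, while the data to correct this have been collected.

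**Working it through.** **1. How many time points did the planning count?** Inputs from the Sample Size section: f=0.20, α=.025, power .95, r=0.50, ε=0.75, N=114. The numbers of groups k and measurements m are not stated. For the group × time interaction, λ = f²·N·m·ε/(1−r), df1 = (k−1)(m−1)ε and df2 = (N−k)(m−1)ε.

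- k=3, m=3, ε=0.75, N=114: λ = 0.04·114·3·0.75/0.5 = 20.52, df1 = 3, df2 = 166.5, power 95.4%. The smallest N is 113, or 114 for equal groups. This reproduces the plan's figure.
- k=3, m=2: with two time points ε can only be 1. The smallest N is 115 (117 for equal groups), and power at 114 is 94.9%.

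The planning thus appears to count three measurements where the model has two. The effect on N is negligible and power at 200 is above 99%, so this shows the inconsistency and is not a power problem.

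**2. Bias in a CHRONIC arm's 6-month mean.** Scores at T0, T1 and T2 were simulated as trivariate normal with unit variance. Loss at T2 followed a logistic model in the T1 score, with worse scores more often lost. The T2 mean was estimated by regression on T0 only, and on T0 and T1, fitted in those observed. r(T0,T2)=0.50 is the plan's value; the rest is assumed.

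| Setting | T0 only | T0 and T1 |
|---|---|---|
| All correlations 0.50, 35% lost, odds ratio 2 per SD | 0.06 SD | 0.00 |
| r(T0,T1)=0.60, r(T1,T2)=0.70, 35% lost, odds ratio 2 | 0.09 SD | 0.00 |
| 25-43% lost, odds ratio 1.5-2.5, r(T1,T2) 0.6-0.8, r(T0,T1) 0.5-0.6 | 0.03-0.19 SD | about 0 |

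Every bias in the T0-only column favours CHRONIC.

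**3. If T1 is missing too.** Suppose half of those lost at T2 also miss T1. Using T1 then reduces the bias from 0.09 to 0.04 SD in the second setting and from 0.057 to 0.022 SD in the first.

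**4. Precision.** With a fraction p missing, the variance of the arm mean is approximately proportional to 1 − p·R², where R² is the share of T2 variance explained by the predictors. With T0 only, R² = 0.50² = 0.25. With T0 and T1, R² = (r02² + r12² − 2·r01·r02·r12)/(1 − r01²).

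- All r=0.50: R² = (0.25 + 0.25 − 0.25)/0.75 = 0.333. Ratio at p=0.35: (1 − 0.35·0.333)/(1 − 0.35·0.25) = 0.883/0.9125 = 0.97, a 3% reduction.
- r01=0.60, r12=0.70: R² = (0.25 + 0.49 − 0.42)/0.64 = 0.50. Ratio: 0.825/0.9125 = 0.90, a 10% reduction.
- r01=0.50, r12=0.80, p=0.43: R² = (0.25 + 0.64 − 0.40)/0.75 = 0.653. Ratio: 0.719/0.8925 = 0.81, a 19% reduction.

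**The case against.** The strongest reply is that the multiple imputation may already use T1. It is described as working from the observed data, T1 is observed data, and a list of imputation predictors commonly belongs in a statistical analysis plan that is not shown. This stands in part. A reader might infer that participants lost after week 12 are handled as though nothing had been seen after baseline, or that imputation adds nothing to the model. The document supports neither, because no sentence restricts the imputation to two time points. What remains is that the article itself fixes a model that leaves T1 out while defending it by its use of the available data.

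Further points, all of which narrow the concern:

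- The rationale says that the method allows inclusion, which is weaker than saying that this model uses everything. It is nevertheless the reason offered for the choice.
- Limiting the randomized contrast to the matched visit is sound, since TAU has no week-12 score. T1 can inform that contrast without becoming one.
- A reader might count the weekly check-ins as omitted outcome data. The CHRONIC Web Application section describes them as self-monitoring: before the next module participants say how the past week went ("they are required to complete a short check-in assessment referring to the preceding week"). They are absent from Table 2 and end when a participant stops opening modules. Leaving them out of the outcome model is no error.
- The Sample Size section attributes the inflation first to TAU dropout, where T1 does not exist. The 43% is a trial-wide allowance and so an upper end for the CHRONIC arms.
- If loss does not depend on week-12 status, there is no such bias.

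**Conclusion.** The concern holds in a limited form. As written, the model excludes the week-12 scores of EGpsych and EGcomp, which does not fit its stated rationale, and the plan leaves open whether the imputation recovers them. Bias follows only if the imputation also omits T1 and loss depends on T1. It is then about 0.06 SD at the plan's own correlation with 35% loss and odds ratio 2, and about 0.03 to 0.19 SD over the wider range. That is not trivial in a trial planned for a small-to-medium effect. Including T1 removes the bias where T1 is observed, and part of it otherwise, and reduces the variance of an arm's mean by about 3-19%.

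The loss rate, the loss mechanism, r(T0,T1) outside the equal-correlation setting and r(T1,T2) are assumptions. The figures are for a CHRONIC arm's mean. Any bias from TAU dropout comes on top and cannot be addressed with T1. The point should be settled in advance; the Results section expects primary end point data to be complete in January 2027, so there is time.

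**What to change.** Keep the matched 6-month contrast as the target and state one of the following:

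1. Add T1 as a third time level estimated only in EGpsych and EGcomp, with an unstructured covariance in place of the random intercept alone. A random intercept forces equal correlations, so it would not let T1 predict T2 better than baseline does.
2. Impute separately by arm, with the T1 outcome scores as predictors in the two CHRONIC arms. The number of completed modules and the last available check-in are optional extra predictors.

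Under either option, do not use TAU data collected after program access. If the imputation was always meant to include T1, one sentence saying so closes the gap, and the rationale sentence should be aligned with the two-level time factor.

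The cost is analysis wording and a slightly richer model in two of the three arms. All the data are already scheduled. The change brings no benefit for TAU dropout.

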### Sample Size

An a priori power analysis was conducted in G*Power (version 3.1.9.7; Erdfelder, Faul, and Buchner) to estimate the sample size required to detect a small-to-medium longitudinal intervention effect in a group comparison. Consistent with common planning approaches for repeated-measures trials, the calculation targeted the group × time interaction under conservative assumptions and serves as an approximation for the primary longitudinal analyses. We assumed an effect size of *f*=0.20, *α*=.025 and statistical power=.95. The correlation among repeated measures was set to *r*=0.50 and the nonsphericity correction to *ε*=0.75 to account for plausible deviations from perfect sphericity. Under these assumptions, G*Power yielded a minimum required sample size of 114. To account for dropout, a target sample size of 200 was prespecified. This inflation reflects the increased risk of dropout in the TAU control group due to the 6-month waiting period and the typical loss to follow-up in digital health trials. The larger sample ensures robustness against assumption violations and maintains adequate power.

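### The two-visit random-intercept model assumes one variance at baseline and 6 months in every arm; the 6-month group contrasts, and under some conditions the pairwise interaction contrasts, can be miscalibrated

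*Protocol article*

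**What the plan says.** All of this is in the Statistical Analysis section of the protocol article.

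- The model has fixed effects for group, "time (baseline vs matched 6-mo assessment), and the group × time interaction". The primary model therefore has two visits.
- The only covariance element named is the random intercept: "A participant-specific random intercept will be included to account for within-person correlation". No residual structure and no visit- or arm-specific variance is given.
- The main test is the interaction: "The group × time interaction will be used to test differential change between conditions".
- After a significant main or interaction effect, "Holm-corrected post hoc tests will be applied to determine the specific time points and group differences". Group contrasts at 6 months are therefore part of the plan.
- If assumptions fail: "If model assumptions are violated, appropriate robust methods will be considered". No method and no trigger is named.
- "Missing data will be handled using multiple imputation, which estimates missing values based on the observed data". The same section also credits the mixed model with using all available outcome data. It does not say whether the model is fitted to imputed or to incomplete data.

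**The concern.** The label of a mixed model for repeated measures normally implies that each visit keeps its own variance. A random intercept plus one residual variance is compound symmetry: equal variance at both visits and across arms. If the spread of a pain or quality-of-life score at 6 months differs from that at baseline, a group contrast at 6 months borrows its standard error partly from the wrong visit. The error is too small if the spread grows and too large if it shrinks.

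This matters because the section centres the randomized comparison on the 6-month assessment, and Study Objectives words the comparisons with TAU as comparisons at named time points. The 6-month contrasts and their confidence intervals are therefore likely to be read as results. Holm adjusts p-values for multiplicity but does not correct the standard errors behind them.

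**Working it through.** **Inputs.** From the protocol: three arms, target 200 (taken as 67/67/66), two visits in the primary model, r = 0.50 (Sample Size). Assumed, because the protocol does not give them: the 6-month/baseline SD ratio k, the SDs by arm, and the dropout rates.

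**The plan's own figure.** Sample Size reports a minimum of 114. With three arms and three time points (neither is stated there), the noncentrality is f²·N·m·ε/(1−r) = 0.04 × 114 × 3 × 0.75 / 0.5 = 20.52, on 3 and 166.5 degrees of freedom. At α = .025 the power is .954. The smallest N is 113, which rounds to 114 for equal arms. The figure is reproduced and does not depend on the point made here.

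**6-month contrast, complete data.** Set the baseline variance to 1 and the 6-month variance to k². The random-intercept model estimates the total variance as the average, (1 + k²)/2. The true variance is k². Arm sizes cancel, so

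model SE / true SE = √((1 + k²)/2) / k, and actual type I error = 2·(1 − Φ(1.96 × ratio)).

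| k (assumed) | SE ratio | 1.96 × ratio | Type I error |
|---|---|---|---|
| 0.8 | 1.132 | 2.219 | 2.7% |
| 1.0 | 1.000 | 1.960 | 5.0% |
| 1.2 | 0.920 | 1.804 | 7.1% |
| 1.3 | 0.892 | 1.749 | 8.0% |
| 1.5 | 0.850 | 1.666 | 9.6% |

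These are for a single contrast, before gating and Holm.

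**6-month contrast after multiple imputation.** Simulation with random loss of 30/30/43% (assumed), 20 imputations and Rubin's rules gives 3.2% at k = 0.8 and 7.6% at k = 1.25 and 1.5, or 7.8% at k = 1.5 with baseline-dependent loss. With the 6-month variance freed, the range is 4.9% to 5.8%. Imputation does not remove the error; freeing the variance does.

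**Interaction, same k in all arms.** With complete data the model reduces to a pooled analysis of change scores, whatever k is. Simulated type I error is 4.4% to 5.8% for k from 0.8 to 1.5, with no systematic error. After imputation it is 4.8% to 5.6%.

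**Interaction, 6-month SDs differing by arm** (assumed 1.5/1.5/1, complete data). Change variance in each CHRONIC arm is 1 + 2.25 − 2(0.5)(1.5) = 1.75; in TAU it is 1 + 1 − 2(0.5) = 1. The pooled value is (67 × 1.75 + 67 × 1.75 + 66 × 1)/200 = 1.5025.

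- EGpsych vs EGcomp: SE ratio √(1.5025/1.75) = 0.927, type I error 6.9%.
- EGpsych vs TAU: true variance 1.75/67 + 1/66 = 0.0413; model variance 1.5025 × (1/67 + 1/66) = 0.0452; SE ratio 1.046, type I error 4.0%.

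Simulation gives 6.9% and 3.9%.

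**Interaction fitted to unimputed data** (EGpsych vs TAU, random loss 30/30/43%, same k in all arms). Type I error is 3.8% at k = 0.8, 5.9% at 1.25 and 7.4% at 1.5.

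**The case against.** The strongest reply has four parts.

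1. **The main test is the interaction, which is sound.** This stands for complete or soundly imputed data with variance changing alike in all arms. A reader might infer that the primary test is invalid; the documents and the calculations do not support that.

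2. **The gate and Holm limit the damage.** This stands in part. In a simulation with no true effect, family-wise error for the Holm-corrected 6-month contrasts was 4.7%, 5.1% and 6.5% at k = 1.2, 1.3 and 1.5 when the interaction or the group main effect opens the gate, and 1.6%, 1.9% and 2.8% when only the interaction does. However, the text lets any significant main effect open the gate. If a time effect alone does so, the figures are 7.4%, 8.4% and 10.9%. If both CHRONIC arms truly differ from TAU and both those contrasts are rejected, Holm leaves EGpsych vs EGcomp at its full nominal level. Confidence intervals are not protected by a gate at all.

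3. **Nothing shows that the variances differ.** This stands. A reader might take three places as the plan's own admission of unequal variance, but none supports it. Sample Size sets a correction "to account for plausible deviations from perfect sphericity", yet sphericity holds trivially with two visits, whatever their variances. Study Design defends the long wait as "preventing artificially low variance caused by very short control periods", which predicts nothing about 6 months against baseline. The entry criterion on distress or disability sets no score cutoff, so a narrowed baseline spread is conjecture.

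4. **Residual structure belongs in the SAP, and the plan allows for robust methods.** A random intercept can be combined with visit-specific residual variances, and the SAP may say so. But the article does fix the random intercept as its covariance element, and its fallback names neither method nor trigger, so the choice would follow sight of the data.

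**Conclusion.** The point holds as a conditional weakness in a specification, not as an error in the primary test. It rests on a homoscedastic residual, which is the usual default but is not stated. If the 6-month and baseline SDs are equal in every arm, nothing is wrong. If they differ by a ratio of 0.8 to 1.5, a single 6-month contrast runs at 2.7% to 9.6% instead of 5%, with the gate and Holm reducing the family-wise effect in most but not all cases. Pairwise interaction contrasts are off by one to two percentage points for the assumed arm-specific SDs, and by up to about 2.4 points in the unimputed fits above.

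A reader might also infer that dropout biases the comparison of CHRONIC with TAU. The documents do not support this. Such bias appears only when the model is fitted to unimputed data with baseline-dependent loss and unequal variances (0.03 to 0.05 baseline SD at k = 1.25 and 1.5). A larger value of −0.14 SD (k = 1.3) needs loss running in opposite directions by arm, which nothing in the protocol suggests. The plan is to impute, and after imputation the simulated interaction shows no such bias.

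**What to change.** Replace the random intercept with an unstructured covariance over the two visits, so that baseline and 6 months each have their own variance. Either let it differ by arm or use robust standard errors. Fix this now, in place of the open promise to consider robust methods, and state that the model is fitted to the multiply imputed data. If the covariance is arm-specific, impute within arm so that the imputed values carry the same structure.

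The cost is one sentence of analysis wording and standard R code. The common unstructured form has three covariance parameters instead of two; the arm-specific form has three per arm, which is negligible against 200 participants. No data, visits or patients are added. According to the Results section, primary end point collection runs to January 2027, so the change can be made before analysis.
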